## 8. Investigational Product

### 8.1. Description of ChAdOx1 nCoV-19

ChAdOx1 nCoV-19 vaccine consists of the replication-deficient simian adenovirus vector ChAdOx1, containing the structural surface glycoprotein (Spike protein) antigens of SARS-CoV-2.

### 8.2. Supply

ChAdOx1 nCoV-19 has been formulated and vialled by AstraZeneca.

The vaccine is stored at 2-8°C in a secure refrigerator, at the clinical site. If stored at this temperature after the first vial puncture, it can be used within up to 48 hours thereafter. All movements of the study vaccines will be documented in accordance with existing standard operating procedure (SOP). Vaccine accountability, storage, shipment and handling will be in accordance with relevant SOPs and forms. To allow for large number of participants to receive the vaccine in a short time period, additional clinic locations may be used. In this instance vaccines will be transported in accordance with local SOP's and approvals as required.

### 8.3. Administration

On vaccination day, the vaccine will be administered intramuscularly into the deltoid of the non-dominant arm (preferably). All participants will be observed in the unit for 1 hour ( $\pm 30$  minutes) after vaccination. During administration of the investigational products, Advanced Paediatric Life Support drugs and resuscitation equipment will be immediately available for the management of anaphylaxis. Vaccination will be performed and the IMPs handled according to the relevant SOPs.

### 8.4. Rationale for selected dose

The dose to be administered in this trial have been selected on the basis of:

1. Pre-clinical immunogenicity data
2. Safety and immunogenicity data from adenoviral vector trials in teenagers and children (Table 2)
3. Safety and immunogenicity data using ChAdOx1 nCoV-19 in adults [24,25]
4. Interim efficacy data from ongoing phase III trials of ChAdOx1 nCoV-19 in adults [26]

Simian adenovirus vector (ChAd63) has been safely administered in adults at doses up to  $2 \times 10^{11}$  vp, with an optimal dose of  $5 \times 10^{10}$  vp, balancing immunogenicity and reactogenicity. MERS001 was the first clinical trial of a ChAdOx1 vectored expressing the full-length Spike protein from a separate, but related betacoronavirus. ChAdOx1 MERS has been given to 31 participants to date at doses ranging from  $5 \times 10^9$  vp to  $5 \times 10^{10}$  vp. Despite higher reactogenicity observed at the  $5 \times 10^{10}$  vp, this dose was safe, with self-limiting AEs and no SARs recorded. The  $5 \times 10^{10}$  vp was the most immunogenic, in terms of inducing neutralising antibodies against MERS-CoV using a live virus assay [24]. Given the immunology findings and safety profile observed with a ChAdOx1 vectored vaccine against MERS-CoV, the  $5 \times 10^{10}$  vp dose was chosen for ChAdOx1 nCoV-19 in adults. Data on immunogenicity of ChAd-vectored homologous prime-boost regimens in children and young adults is limited. Single dosing at  $1 \times 10^{11}$  has been shown to be immunogenic [27], with serological responses similar to those seen in adults.

Phase I/II clinical trial data of ChAdOx1 nCoV-19 in adults demonstrate that when given as a homologous prime-boost, a dose of  $5 \times 10^{10}$  vp demonstrates an acceptable side effect profile (most commonly pain,

feeling feverish, chills, muscle ache, headache, malaise) which can be ameliorated with the use of prophylactic paracetamol. [24] No SAEs related to the vaccination were noted, and immunogenicity (neutralising antibody responses) were present in 100% post boost, which correlated strongly with antibody levels measured by ELISA. Interim analyses of phase III data from an ongoing adult study suggest that a LD/SD regimen (where low dose is approximately half the standard dose of  $5 \times 10^{10}$  vp) may have a greater efficacy than SD/SD regime, however confidence intervals for efficacy estimates of these two groups overlap [26].

Given that a SD/SD ( $5 \times 10^{10}$  vp homologous prime-boost) regimen of ChAdOx1 nCoV-19 now has emergency approval for use in adults in the UK (as of December 2020) and similar doses of a ChAdOx viral vector have previously been administered to children and infants, this study will explore the same dosing regimen in children. However, evidence [unpublished data] suggests that a longer interval between doses of up to 12 weeks may be associated with acceptable immunogenicity, therefore this study will explore 2 different boosting strategies, one 4 weeks post-prime and one 12 weeks post-prime. Minimising environmental contamination with genetically modified organisms (GMO)

The study will be performed in accordance with the current version of the UK Genetically Modified Organisms (Contained Use) Regulations. Approved SOPs will be followed to minimise dissemination of the recombinant vectored vaccine virus into the environment. GMO waste will be inactivated according to approved SOPs.

### **8.5. Control Vaccine**

Participants who are allocated to the control groups will receive two injections of MenB vaccine instead of ChAdOx1 nCoV-19.

Participants will be blinded as to which intervention they are receiving. A vaccine accountability log of MenB will be maintained. There will be no additional labelling of these vaccines beyond their licensed packaging.

MenB will be stored in a locked (or access controlled) refrigerator (2°C – 8°C) at the sites, as per SmPC.

### **8.6. Compliance with Trial Treatment**

All vaccinations will be administered by the research team and recorded in the CRF. The study medication will be at no time in the possession of the participant and compliance will not, therefore, be an issue.

### **8.7. Accountability of the Trial Treatment**

Accountability of the IMP and control vaccine will be conducted in accordance with the relevant SOPs.

### **8.8. Concomitant Medication**

As set out by the exclusion criteria, participants may not enter the study if they have received: any vaccine in the 30 days prior to enrolment or there is planned receipt of any other vaccine within 30 days of each vaccination, any investigational product within 30 days prior to enrolment or if receipt is planned during the study period, or if there is any use of immunosuppressant medication within 6 months prior to enrolment or if receipt is planned at any time during the study period ( except topical steroids and short course of low dose steroids < 14 day). Participants will be advised to take paracetamol post-vaccination only if they develop clinical symptoms, and these should be recorded in the e-diary. They will not be advised to take prophylactic paracetamol.

## 8.9. Provision of Treatment for Controls

If any other vaccine shown to be efficacious at preventing COVID-19 disease is licensed for this age group during the course of this study, then participants will not be disadvantaged by their participation in the trial. Unblinding will be offered upon discussion, to facilitate participation in any national immunisation programme that is implemented. All those in the control group will be offered a full course of the IMP (ChAdOx1 nCoV-19) at the end of the study if they are not eligible for a vaccine under national immunisation guidelines, should it be approved for use in the age group. All those in the intervention arms will be offered Bexsero at the end of the study.

## 9. Assessment of safety

Safety will be assessed by the frequency, incidence and nature of AEs, SAEs and AESIs arising during the study. Events recorded on the diary card will be used for D7 and subsequent safety reviews by the CI, relevant investigators, DSMB and MHRA, and de-identified made available to AstraZeneca. Solicited (up to day 7) and unsolicited (up to day 28) events will be recorded on diary cards.

### 9.1. Adverse Event (AE)

An AE is any untoward medical occurrence in a participant, which may occur during or after administration of an IMP and does not necessarily have a causal relationship with the intervention. An AE can therefore be any unfavourable and unintended sign (including any clinically significant abnormal laboratory finding or change from baseline), symptom or disease temporally associated with the study intervention, whether or not considered related to the study intervention.

### 9.2. Adverse Reaction (AR)

An AR is any untoward or unintended response to an IMP. This means that a causal relationship between the IMP and an AE is at least a reasonable possibility, i.e., the relationship cannot be ruled out. All cases judged by the reporting medical Investigator as having a reasonable suspected causal relationship to an IMP (i.e. possibly, probably or definitely related to an IMP) will qualify as AR.

Adverse events that may be related to the IMP are listed in the Investigator's Brochure for ChAdOx1 nCoV-19 and the [SmPC](#) for Meningococcal Group B vaccine (Bexsero®).

### 9.3. Serious Adverse Event (SAE)

An SAE is an AE that results in any of the following outcomes, whether or not considered related to the study intervention.

- Death
- Life-threatening event (i.e., the participant was, in the view of the Investigator, at immediate risk of death from the event that occurred). This does not include an AE that, if it occurred in a more severe form, might have caused death.
- Persistent or significant disability or incapacity (i.e., substantial disruption of one's ability to carry out normal life functions).

- Hospitalisation or prolongation of existing hospitalisation, regardless of length of stay, even if it is a precautionary measure for continued observation. Hospitalisation (including inpatient or outpatient hospitalisation for an elective procedure) for a pre-existing condition that has not worsened unexpectedly does not constitute a serious AE.
- An important medical event (that may not cause death, be life threatening, or require hospitalisation) that may, based upon appropriate medical judgment, jeopardise the participant and/or require medical or surgical intervention to prevent one of the outcomes listed above. Examples of such medical events include allergic reaction requiring intensive treatment in an emergency room or clinic, blood dyscrasias, or convulsions that do not result in inpatient hospitalisation.
- Congenital malformations or birth defects – structural, functional, genetic or behavioural anomalies, including metabolic disorders that occur during fetal development and can be diagnosed prenatally, at birth or later in life

#### **9.4. Serious Adverse Reaction (SAR)**

An AE that is both serious and, in the opinion of the reporting Investigator or Sponsors, believed to be possibly, probably or definitely due to an IMP or any other study treatments, based on the information provided.

#### **9.5. Suspected Unexpected Serious Adverse Reaction (SUSAR)**

A SAR, the nature and severity of which is not consistent with the information about the medicinal product in question set out in the IB.

#### **9.6. Expectedness**

No IMP related SAEs are expected in this study. All SARs will therefore be reported as SUSARs.

#### **9.7. Foreseeable Adverse Reactions:**

The foreseeable ARs following vaccination with ChAdOx1 nCoV-19 include injection site pain, tenderness, erythema, warmth, itch, swelling, fever/feverishness, chills, joint pain, muscle pain, fatigue, headache, malaise, nausea and vomiting.

#### **9.8. Adverse Events of Special Interest (AESI)**

##### **Severe COVID-19 cases**

Severe COVID-19 disease will be defined using clinical criteria as outlined by the RCPCH [35]. Detailed clinical parameters will be collected from medical records and aligned with agreed definitions as they emerge. These are likely to include, but are not limited to, oxygen saturation, need for oxygen therapy, respiratory rate, need for ventilatory support, imaging and blood test results, amongst other clinically relevant parameters.

Acute respiratory distress, pneumonitis, acute cardiac injury, arrhythmia, septic-shock like syndrome and acute kidney injury related with COVID-19 disease will be monitored from medical records review of hospitalised participants.

## PIMS-TS

The Royal College of Paediatrics and Child Health has outlined a case definition for PIMS-TS.

1. A child presenting with persistent fever, inflammation (neutrophilia, elevated CRP and lymphopaenia) and evidence of single or multi-organ dysfunction (shock, cardiac, respiratory, renal, gastrointestinal or neurological disorder) with additional features (Table 8) This may include children fulfilling full or partial criteria for Kawasaki disease.
2. Exclusion of any other microbial cause, including bacterial sepsis, staphylococcal or streptococcal shock syndromes, infections associated with myocarditis such as enterovirus (waiting for results of these investigations should not delay seeking expert advice).
3. SARS-CoV-2 PCR testing may be positive or negative

Table 8: Additional features associated with PIMS-TS [RCPCH, 2020]

| Clinical                                                                                                                                                                                                                                                                                                                                                            | Laboratory                                                                                                                                                                                                                                                                                                                                                                                                                         | Imaging and ECG                                                                                                                                                                                                                                                                                                                       |
|---------------------------------------------------------------------------------------------------------------------------------------------------------------------------------------------------------------------------------------------------------------------------------------------------------------------------------------------------------------------|------------------------------------------------------------------------------------------------------------------------------------------------------------------------------------------------------------------------------------------------------------------------------------------------------------------------------------------------------------------------------------------------------------------------------------|---------------------------------------------------------------------------------------------------------------------------------------------------------------------------------------------------------------------------------------------------------------------------------------------------------------------------------------|
| All:
Persistent fever >38.5

Most:
Oxygen requirement
Hypotension

Some:
Abdominal pain
Confusion
Conjunctivitis
Cough
Diarrhoea
Headache
Lymphadenopathy
Mucus membrane changes
Neck swelling
Rash
Respiratory symptoms
Sore throat
Swollen hands and feet
Syncope
Vomiting | All:
Abnormal fibrinogen
Absence of potential causative organisms
High CRP
High D-Dimers
High ferritin
Hypoalbuminaemia
Lymphopenia
Neutrophilia in most – normal neutrophils in some

Some:
Acute kidney injury
Anaemia
Coagulopathy
High IL-10/6
Neutrophilia
Proteinuria
Raised CK, LDH, triglycerides
Raised troponin
Thrombocytopenia
Transaminitis | Echo and ECG – myocarditis, valvulitis, pericardial effusion, coronary artery dilatation

CXR – patchy symmetrical infiltrates, pleural effusion

Abdo USS – colitis, ileitis, lymphadenopathy, ascites, hepatosplenomegaly

CT chest – as for CXR – may demonstrate coronary artery abnormalities if with contrast |

The Safety Platform for Emergency vaccines has outlined AESI guidelines for the development of COVID-19 vaccines. Whilst these may be more geared towards adult trial participants, they are likely to be relevant to some of the older participants in this trial.

Following updated safety guidance from the JCVI and MHRA dated 8th April 2021 [39], addition of Cerebral Venous Sinus Thrombosis, Heparin-Induced Thrombocytopenia and major thrombosis with concurrent thrombocytopenia were added to the AESIs of special interest list. Participants have been asked to be alert to the following symptoms in the first 28 days following vaccination and to seek medical attention if they occur. This warning has been inserted into patient information sheets as appropriate.

- Sudden severe headache that does not improve with usual pain killers or is getting worse
- An unusual headache which seems worse when lying down or bending over, or may be accompanied by blurred vision, nausea and vomiting, difficulty with speech, weakness, drowsiness or seizures
- New and unexplained pinprick bruising or bleeding
- Shortness of breath, chest pain, leg swelling or persistent abdominal pain

Table 9: SPEAC COVID-19 vaccine AESIs of special interest

|                |                                                                                                                                                                                                                                                                                                     |
|----------------|-----------------------------------------------------------------------------------------------------------------------------------------------------------------------------------------------------------------------------------------------------------------------------------------------------|
| Neurological   | Isolated anosmia/ageusia*
Guillain-Barre Syndrome
Encephalitis
Encephalopathy
Brain haemorrhage
Seizure
ADEM
Myelitis                                                                                                                                                          |
| Haematological | Thrombosis**
Stroke
Coagulopathy
Pulmonary embolus
Other thromboembolism
Ischemia
Endothelial dysfunction
Thrombocytopenia***
Eosinophilia****
Cerebral Venous Sinus Thrombosis
Heparin-Induced Thrombocytopenia
Major thrombosis with concurrent thrombocytopenia |
| Cardiac        | Myocarditis
Arrhythmia
Heart failure                                                                                                                                                                                                                                                          |

|                                                                                                                                                                                                                                                                                                                                                                                                                                                                                                                                                                                                                                                                                     |                                                                                 |
|-------------------------------------------------------------------------------------------------------------------------------------------------------------------------------------------------------------------------------------------------------------------------------------------------------------------------------------------------------------------------------------------------------------------------------------------------------------------------------------------------------------------------------------------------------------------------------------------------------------------------------------------------------------------------------------|---------------------------------------------------------------------------------|
|                                                                                                                                                                                                                                                                                                                                                                                                                                                                                                                                                                                                                                                                                     | Acute coronary syndrome
Ruptured aneurysm
Sudden cardiac death            |
| Dermatological                                                                                                                                                                                                                                                                                                                                                                                                                                                                                                                                                                                                                                                                      | Chilblain
Cutaneous vasculitis
Erythema multiforme
Alopecia            |
| Gastrointestinal                                                                                                                                                                                                                                                                                                                                                                                                                                                                                                                                                                                                                                                                    | Acute liver injury †††
Gastrointestinal ischaemia/thrombosis
Appendicitis |
| Respiratory                                                                                                                                                                                                                                                                                                                                                                                                                                                                                                                                                                                                                                                                         | ARDS††                                                                          |
| Renal                                                                                                                                                                                                                                                                                                                                                                                                                                                                                                                                                                                                                                                                               | Acute kidney injury                                                             |
| Other                                                                                                                                                                                                                                                                                                                                                                                                                                                                                                                                                                                                                                                                               | COVID-19 disease†
Vasculitides
Anaphylaxis                                |
| 
*In the absence of COVID-19
 
** Excluding superficial thrombophlebitis (including line-associated)
 
*** G3 or above
 
**** This will be used as a marker skewed Th2 responses and will be routinely monitored in participants attending the COVID-19 Pathway and follow-up visits. Only G2 and above.
 
† In particular, any occurrence of suspected vaccine associated enhanced disease (VAED) as defined by most recent Brighton Collaboration Case Definition
 
†† In the absence of an infective aetiology (including COVID-19)
 
††† As defined in Hy's Law (see Cases falling under the Hy's Law should be reported as SAEs. 0)
 |                                                                                 |

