### 7.3. Blood tests

Safety bloods will be taken for a subset of up to 40 participants in groups 3 and 4, as outlined in tables 5b and 5d. These will include a full blood count, urea and electrolytes, liver function tests, CRP, clotting screen and D-dimer. Reference ranges will be in accordance with local NHS guidelines. Abnormalities occurring outside this range will be graded in severity and those scoring a grade 3 or above will be classified as an AE.

Immunology; Immunogenicity will be assessed by a variety of immunological assays. This may include antibodies to SARS-CoV-Spike and non-Spike antigens by ELISA, ex vivo ELISpot assays for interferon gamma and flow cytometry assays, neutralising and other functional antibody assays and B cell analyses, virus neutralising Ab (NAb) assays against live and/or pseudotype SARS-CoV-2 virus. Other exploratory immunological assays including cytokine analysis and other antibody assays, DNA analysis of genetic polymorphisms potentially relevant to vaccine immunogenicity and gene expression studies amongst others may be performed at the discretion of the Investigators. Further exploratory immunology assays may be performed at the discretion of the Investigators on HIV and non-HIV cohorts, including, but not limited to: T cell Proliferative responses to SARS-CoV-2 antigen; T cell cross-reactivity to circulating common cold coronaviruses; Multiparameter immunophenotyping by CyTOF; BCR and TCR repertoire analysis; Serum analysis by Luminex (including inflammatory, anti-inflammatory and adaptive cytokines, chemokines, growth factors and antimicrobial proteins); HIV viral reservoir; amongst others.

Collaboration with other specialist laboratories in the UK, Europe and outside of Europe for further exploratory tests may occur. This would involve the transfer of serum or plasma, PBMC and/or other study samples to these laboratories, but these would remain anonymised. Informed consent for this will be gained from participants. This would be in line with the national guidance and policy for submitting samples for testing at reference labs. Immunological assays will be conducted according to local SOPs.

Participants or their parent/guardian will be informed that there may be leftover samples of their blood (after all testing for this study is completed), and that such samples may be stored indefinitely for possible

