#### 7.4.3. Subsequent visits:

Follow-up visits will take place as per the schedule of attendances outlined in Tables 5a-d, with their respective windows. Safety bloods will be conducted in a subset of participants aged 6-11 years (to be determined by the sites); up to 40 participants will be allocated to have safety bloods taken at one of V3a, V3b, V4a or V4b, resulting in 6 study bloods being taken for this subgroup.. Participants will also have safety bloods taken on the day of the booster. This is to ensure accurate interpretation of any abnormal safety blood findings.

Participants will be assessed for local and systemic adverse events, interim history, physical examination, if required, review of diary cards (paper or electronic) and blood tests at these time points as detailed in the schedule of attendances. Blood will also be taken for immunology purposes and a booster vaccination given at Visit 2.

If participants experience adverse events (laboratory or clinical), which the investigator (physician), CI and/or DSMB chair determine necessary for further close observation, the participant may be admitted to an NHS hospital for observation and further medical management under the care of the Consultant on call.

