#### 7.4.5. 'Positive Pathway' for SARS CoV-2 infection

The parents or guardians of participants who are under 16/participants who are 16 and over who test positive for SARS CoV-2 infection in the community during the follow-up period will be instructed to contact the study team, who will then log the case on the eCRF.

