## 10. STATISTICS

### 10.1. Sample size

The total sample size of this trial will be 261 with 60 participants in ChAdOx1 nCoV-19 groups and 15 in each of the Meningococcal B vaccine groups for Groups 1 and 2. With a sample size of 60 participants, the probability of observing at least one participant with an adverse event will be more than 90%, if the underlying incident rate is 5%. The analysis for primary endpoints will be descriptive and there has been no formal power calculation to determine the sample size of the trial. The numbers have been therefore chosen based on practical constraints.

Following the updated safety guidance from the JCVI on 8th April 2021 [39], no more participants have been recruited. All the participant aged 6-11 years who randomised to group3 (boosted at 28 days) will be boosted at 112 days. The planned sample size of 75 has been achieved in Groups 1 and 2, and recruitment in Groups 3 and 4 stands at 55 and 56 respectively. As Groups 3 and 4 will both be boosted at D112 post prime, the two groups will be combined for all the safety and immunogenicity analysis. Therefore, the analysis of the younger age cohort will have increased power.

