##### 10.1.1. Safety and reactogenicity

All SAEs will be presented for each group using descriptive analyses, including any evidence of disease enhancement, hospital admissions and cases of suspected PIMS-TS.

Counts and percentages of each local and systemic solicited adverse reaction from diary cards, and all unsolicited AEs, and SAEs of special interest will be presented for each group.

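### Eosinophilia, the protocol's marker of Th2 skewing, is said to be routinely monitored, but at least 221 of 261 children have no scheduled eosinophil count and none is scheduled after infection

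*Protocol*

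**What the plan says.** - **Monitoring claim (9.8, footnote to Table 9).** Eosinophilia is the marker for Th2 skewing, counted from Grade 2, and "will be routinely monitored in participants attending the COVID-19 Pathway and follow-up visits".
- **Infection pathway (7.4.5).** Families of children who test positive in the community contact the study team, "who will then log the case on the eCRF". No visit or blood sample is described.
- **Blood counts (7.3).** "Safety bloods will be taken for a subset of up to 40 participants in groups 3 and 4". On content: "These will include a full blood count, urea and electrolytes, liver function tests, CRP, clotting screen and D-dimer".
- **Timing (7.4.3).** "up to 40 participants will be allocated to have safety bloods taken at one of V3a, V3b, V4a or V4b", and "Participants will also have safety bloods taken on the day of the booster". Tables 5c and 5d set the windows at D2-4 and D7-12 after the booster. Tables 5a and 5b, for the 12-17 year olds, have no safety-bloods row.
- **Use of the data.** Section 9 says safety is judged by, among other things, the frequency and incidence of AESIs, and 9.10 collects Table 9 AESIs for the whole trial. Section 10.1.1 gives counts and percentages: all unsolicited AEs and "SAEs of special interest will be presented for each group". Section 10.2 puts every vaccinated child in the safety analysis.

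**The concern.** Eosinophilia is a laboratory finding that can be silent. If the blood is not drawn, it is not found. The footnote tells the reader that the trial looks for it routinely, both in infected children and at follow-up, while the schedule looks for it in a small subset around the booster only.

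Disease enhancement is part of primary endpoint (d), and this footnote is the only place where the protocol names a marker of Th2 skewing. If no eosinophilia is reported, a reader who trusts the footnote will take that as evidence from all 261 children, including those who were infected. For adolescents, for infected children, and for the time between the prime and the booster visit, the scheduled tests supply no such evidence.

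**Working it through.** **Is a count scheduled where the footnote says it is?**

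| Occasion | Scheduled full blood count? | Source |
|---|---|---|
| After a positive SARS-CoV-2 test | No; contact and eCRF entry | 7.4.5 |
| Group 1: D28, D56, D182, D364 | No; immunogenicity bloods only | Table 5a |
| Group 2: D84, D112, D140, D364 | No; immunogenicity bloods only | Table 5b |
| Groups 3 and 4: D28 (Group 3 only), D84, D140, D364 | No; immunogenicity bloods only | Tables 5c, 5d |
| Groups 3 and 4: booster day (D112) | Subset, 20 per group | Tables 5c, 5d |
| Groups 3 and 4: D2-4 or D7-12 after booster | Subset, 10 per group at each | Tables 5c, 5d |

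The assays listed in 7.3 for the immunology samples do not include a blood count.

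One sentence points the other way. Section 7.4.2 mentions safety bloods at D0 and refers to Tables 5a and 5b, which contain no such row. Even if those samples were taken, they belong to the enrolment visit at which the prime is given. They could not serve as follow-up or as monitoring after infection.

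**How many children have no scheduled count?** Section 10.1: "The total sample size of this trial will be 261".
- 75 + 75 + 56 + 55 = 261.
- 261 − 40 = 221, and 221/261 = 84.7%. This is a minimum, because 40 is a ceiling.
- It comprises all 150 in Groups 1 and 2 (60 + 60 = 120 given ChAdOx1) and at least 111 − 40 = 71 in Groups 3 and 4.

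**The protocol's own detection figure.** Section 10.1 states more than 90% probability of at least one event at n = 60 and a 5% rate. 1 − 0.95^60 = 0.954, so it reproduces. It does not carry over to an event seen only in tested children.

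**What would zero events show?** ChAdOx1 recipients: 60 + 60 + 90 = 210. How many of the 40 receive ChAdOx1 is not stated. *Assumption:* the subset follows the 4:1 allocation, 40 × 0.8 = 32; range 28 to 36. The one-sided 95% upper bound for 0/n is 1 − 0.05^(1/n), and the detection probability is 1 − 0.95^n.

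| ChAdOx1 denominator | Upper bound for 0/n | P(at least one event at 5%) |
|---|---|---|
| 28 | 10.1% | 0.762 |
| 32 | 8.9% | 0.806 |
| 36 | 8.0% | 0.842 |
| 40 (all tested on ChAdOx1) | 7.2% | 0.871 |
| 210 (mostly untested) | 1.4% | not applicable |

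If the true rate were 5% and found only in the 32 tested, the expected count is 0.05 × 32 = 1.6. Over 210 that is 0.8%.

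**Thresholds.** Section 7.3 makes a laboratory abnormality an AE only from Grade 3, while the footnote counts eosinophilia from Grade 2. On Table 11, a Grade 2 count (2.0 to 5.0 ×10⁹/L) is an AESI under one rule and not an AE under the other, even in the tested children.

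**The case against.** Several stronger readings are tempting, and the documents do not support them.

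- *The same failure applies to thrombocytopenia and Hy's-law liver injury.* A reader might infer this because both are in Table 9. The footnotes give a Grade 3 threshold for one and a case definition for the other; neither promises testing. Collecting AESIs throughout the trial is ordinary event reporting. These two share only the limit that silent cases outside the subset would be missed. Overt cases can surface through clinically relevant tests (7.1) or medical records.
- *The plan prescribes a false 0% eosinophilia for each group.* It does not. Section 10.1.1 speaks of SAEs of special interest, not all AESIs, and 9.11 sends AESIs that are not SAEs to the DSMB reports. Section 10.2 defines who is in the safety population; it does not say that an untested child counts as negative. Table denominators may properly be settled in the SAP, which is not to hand.
- *Endpoint (d) cannot be assessed.* It does not rest on eosinophils. Severe and medically attended COVID-19 is followed through notes review (7.4.6, 9.8), and suspected enhanced disease has its own case definition.
- *The limit is hidden.* Primary endpoint (e) is openly tied to the D2 and D7 post-boost safety bloods, and 7.3 and 7.4.3 say who is tested.

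All of this narrows the point, and it removes any claim about a prescribed percentage. It does not rescue the footnote. Stating the true schedule elsewhere is what makes the footnote wrong, and discretionary tests and hospital notes are not routine monitoring of a silent finding.

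**Conclusion.** The point holds for eosinophilia. The protocol claims routine monitoring that its schedule does not contain: no count after infection, none between the prime and booster day, none at the routine follow-up visits, and none in any 12-17 year old, subject only to the D0 sentence in 7.4.2 that its own tables do not bear out. The count of at least 221 of 261 needs no assumption beyond the stated group sizes and the ceiling of 40.

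The bounds do rest on an assumption, the 4:1 split of a subset that 7.4.3 leaves to the sites. The conclusion is not sensitive to it: even if all 40 tested children had ChAdOx1, the bound is 7.2%, about five times the 1.4% that the full denominator would suggest (7.2/1.4 = 5.1). The 1.4% shows what a careless denominator would imply; it is not an analysis that the protocol specifies. Absence of eosinophilia outside the subset should be called an uninformative zero, not evidence against Th2 skewing.

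**What to change.** Reconcile the eosinophilia footnote in 9.8 with 7.3, 7.4.2, 7.4.3, 7.4.5 and Tables 5a-5d. In the same pass:

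- correct the cross-references: 7.4.2 sends D0 safety bloods to Tables 5a and 5b, and 7.3 cites 5b and 5d, while the safety-bloods rows are in 5c and 5d;
- reconcile the Grade 2 AESI threshold with the Grade 3 laboratory AE rule in 7.3.

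If the schedule stands as written:

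1. Remove the routine-monitoring statement and say who has scheduled counts and when.
2. Report laboratory-detected eosinophilia with the children actually tested as the denominator, and enter Groups 1 and 2 as not assessed by schedule.
3. List clinically ascertained cases separately.
4. Do not state in reports that Th2 skewing was monitored after infection.

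The cost is wording in the footnote and in the safety reporting text, with no change to visits or procedures. The downside is that the stated safety evidence becomes less favourable.
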